#### Primary analysis: EXP versus TAU

In the primary analysis, outcomes of the two treatment conditions will be compared using repeated measures analysis (GLM), with the number of sessions as a covariate. In this analysis, each follow-up measurement will be compared separately to the baseline measurement. Since in this design patients are nested within therapists, these nested data will also be examined in a multilevel analysis, controlling for therapist variation. The number of sessions will be included as a covariate.

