### Patients at risk of failure

When patients benefit from therapy, this generally happens in an early phase of treatment [17,18]. Several authors have looked at the issue of whether 'early symptom change', as experienced by the patient, is a feasible predictor of a good outcome in given patient-therapist combinations [9,15,19,20]. Lambert [9] found that in 84% of early changers subsequent therapy was positive; approximately 25% of the clients actually underwent a dramatically rapid improvement that –usually- led to sustained recovery. Howard et al. [14] found not only that change occurred earlier rather than later in the course of treatment, but also that the absence of early change diminished the probability of symptom reduction and improved well-being at the end of treatment. Brown et al. [12] found that when there is no improvement after three sessions generally no improvement will be achieved over the entire course of treatment; they also found that patients who report deterioration by the third session have a drop-out risk twice as high as patients who report improvement. An improvement in well-being in the first 3–5 sessions therefore has predictive value for the course of therapy. Also more specific patterns of early change, slow and fast have been identified [21].

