### The role of the alliance

Repeatedly, the literature has shown that the therapeutic alliance is an important factor in psychotherapy [36]. There is some evidence that various measures of early (relationship-related) interpersonal in-session processes account for at least 8% to 14% of explained outcome variance [36,37].

Patient ratings of the therapeutic relationship between Sessions 3 and 5 provide reasonable predictions of treatment outcome [38]and a low score for the quality of the alliance emerged as a predictor for premature termination of treatment [39,40].

Though change and alliance are mutually connected and hard to separate, analyses have been performed to try to disentangle this relation [41-43], indicating that both phenomena have separate influences on outcome. So, apart from ‘early change’, the alliance has emerged from patient-focused research as a second predictor of outcome.

There are indications that timely detection of a poor working alliance results in better outcomes and that feedback about this topic can initiate improvement/remediation of the relationship, preventing stagnation in the therapeutic process and identifying potential drop-out in good time [31,42,44].

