### Data analysis

#### Sample size calculation

With two groups of 90 patients, an alpha of 0.05 (one-tailed), an effect size of about 0.3 on the Global Severity Index at 12 weeks (mean EXP group = 1.0; mean TAU = 1.3; standard deviation at week 12 is 0.80) can be detected with a statistical power of 80%. Analysis will be performed according to the intention to treat principle.

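### By default, the primary repeated-measures GLM omits patients who lack a score it needs; this fits poorly with the declared intention to treat and can understate the feedback effect if drop-out differs by arm

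*Protocol article*

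**What the plan says.** All references are to the protocol article.

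- **Sample size calculation** gives the principle: "Analysis will be performed according to the intention to treat principle". The planning values are for the Global Severity Index (GSI) at 12 weeks: "mean EXP group = 1.0; mean TAU = 1.3; standard deviation at week 12 is 0.80", with 90 patients per group and "an alpha of 0.05 (one-tailed" level.
- **Primary analysis: EXP versus TAU** names the method: "outcomes of the two treatment conditions will be compared using repeated measures analysis (GLM), with the number of sessions as a covariate". Each later measurement is set against baseline separately. A multilevel analysis is added because patients are nested within therapists.
- **Patients at risk of failure** reports from a cited study that "patients who report deterioration by the third session have a drop-out risk twice as high as patients who report improvement".
- **The role of the alliance** says there are indications that feedback on the alliance can help in "preventing stagnation in the therapeutic process and identifying potential drop-out in good time".
- **Procedures and time points** schedules the BSI at baseline and after 6, 12, 18 and 24 weeks of treatment, again when treatment ends, and three months later.

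The article gives no expected drop-out rate.

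**The concern.** A classical repeated-measures GLM works on complete rows. The sentence about separate comparisons with baseline can be read in two ways:

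- **One model over all occasions, with contrasts against baseline.** A patient missing any occasion is left out.
- **A separate model for each pair of occasions.** A patient missing week 12 is left out of the week-12 comparison, and the week-6 score that might have foretold the loss is not used.

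Either way, the estimate describes patients who supplied the needed scores, whereas research question 1 concerns the treated population as a whole.

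This matters if loss of scores is related to outcome and the relation differs by arm. The article ties drop-out to early worsening. Only the EXP arm has a procedure that picks up poor progress or a poor alliance and checks that the client will come back (Session rating scale; Interpretation and consequences of the ORS and SRS scores). If that procedure keeps worsening patients in measurement while TAU loses them, TAU's remaining patients look too well and the contrast shrinks. Feedback that worked as intended would then be penalised by its own primary analysis.

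**Working it through.** **1. Reproduce the stated power.** Inputs from Sample size calculation: n = 90 per arm, difference 1.3 − 1.0 = 0.30, SD 0.80, one-sided 5%.

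Power = Φ(0.30 / (0.80·√(2/n)) − 1.645). For n = 90 this is Φ(2.516 − 1.645) = 0.808, which agrees with the stated 80%. The same formula requires 88 per arm, so there is almost no slack.

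**2. Precision.** Let a fraction f of patients supply week 12. A comparison of completers has n = 90f. A likelihood analysis that also uses an always-observed week-6 score, with correlation ρ to week 12, has approximate effective size 90 / [(1 − ρ²)/f + ρ²]. Both are for unadjusted week-12 means, and ρ is assumed to be 0.5-0.7.

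| Loss | Completers: n, power | Likelihood, ρ = 0.5: effective n, power | Likelihood, ρ = 0.7: effective n, power |
|---|---|---|---|
| 20% | 72, 0.727 | 75.8, 0.747 | 79.8, 0.766 |
| 30% | 63, 0.677 | 68.1, 0.707 | 73.9, 0.737 |

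Power falls by 8 points (0.808 to 0.727) at 20% loss and by 13 points (0.808 to 0.677) at 30%. The choice of method accounts for about 2-4 and 3-6 of those points. The rest is the price of missing data under any method.

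**3. Bias.** Simulation with 1,000,000 patients per arm.

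- From the article: week-12 means 1.0 and 1.3, SD 0.80, and a doubled drop-out risk after early worsening.
- Assumed: baseline mean 1.7 in both arms; week-6 means halfway to week 12; correlation ρ = 0.5 or 0.7 between adjacent visits and ρ^1.5 between baseline and week 12; base drop-out p = 10, 20 or 30%, becoming 2p if the week-6 GSI exceeds baseline.

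The true difference in change is 0.300 in favour of EXP. Each cell gives the results for ρ = 0.5 / ρ = 0.7.

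| p | Completers, doubled in both arms | Completers, doubled in TAU only | Likelihood, TAU only, week 6 seen | Likelihood, TAU only, week 6 not seen |
|---|---|---|---|---|
| 10% | 0.299 / 0.298 | 0.279 / 0.281 | 0.302 / 0.300 | 0.290 / 0.287 |
| 20% | 0.293 / 0.294 | 0.243 / 0.255 | 0.298 / 0.299 | 0.270 / 0.268 |
| 30% | 0.290 / 0.288 | 0.199 / 0.219 | 0.303 / 0.302 | 0.250 / 0.243 |

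- Doubled in both arms: the largest error is 0.300 − 0.288 = 0.012. Each arm's own change looks better by about 0.02-0.10, but the two shifts nearly cancel.
- Doubled in TAU only: the understatement runs from (0.300 − 0.281)/0.300 = 6% to (0.300 − 0.199)/0.300 = 34%.
- Likelihood model, week 6 observed before departure: about 0.30. This recovery is partly built in, because simulated drop-out depends only on scores the model sees.
- Likelihood model, departure before week 6: 0.243-0.290, so 3-19% of the effect is still lost.

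**4. Sensitivity to the assumptions.** With baseline mean 1.6 and compound-symmetric or AR(1) correlations of 0.5 or 0.7, TAU-only doubling gives completers 0.234-0.279 at p = 15-20% and 0.176-0.238 at p = 30%. The direction is the same. The upper end is set by the assumed correlations: (0.300 − 0.176)/0.300 = 41% in the most extreme case.

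**The case against.** A reader might infer that the plan analyses only patients with complete scores and that its effect estimate is therefore biased. The article does not support that, for these reasons:

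- **Complete cases are not stated.** Omission of incomplete records is the usual behaviour of the named method, not a rule in the text. The same GLM could be run on imputed data, and a missing-data rule may stand in an analysis plan not shown. Its absence here is no finding. Under the pairwise reading, a patient needs only two scores, not a full set.
- **The multilevel analysis might use incomplete records** if fitted to the repeated scores. That is possible, but the stated purpose is therapist variation and no occasion level is described. It can be neither counted as a repair nor ruled out.
- **A link between drop-out and arm is not established.** The cited doubling concerns deterioration, not arm, and leaving therapy rather than loss of questionnaires; a measurement at the end of treatment is planned. The article words the effect of alliance feedback on drop-out cautiously and calls its effect on alliance and outcome unclear. With equal drop-out behaviour in the two arms, the bias is negligible. The 6-34% needs feedback to remove the whole excess risk in EXP and none of it in TAU.
- **Intention to treat is not flatly contradicted.** Analysis by allocated arm and treatment of missing scores are separate questions. The article's explicit departure, exclusion of patients after the two assessment sessions (Randomisation), is another matter that this point does not touch.

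These objections remove any claim of certain bias. They leave a primary method that, used in its ordinary way, discards outcome data that a readily available alternative would use.

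**Conclusion.** The point holds in conditional form. Unless missing scores are dealt with elsewhere, the named GLM omits patients from each comparison for which they lack a score and wastes their other scores, which fits poorly with the declared intention-to-treat analysis.

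- **Precision:** a modest loss attributable to the method, about 2-6 points of power at 20-30% missing.
- **Bias:** close to zero if worsening patients leave at the same rate in both arms. It is roughly 6-34% towards no effect if feedback retains worsening patients whom TAU loses. The trial's own rationale makes that pattern plausible without establishing it.

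Only the week-12 means, the SD and the doubled risk come from the article. The drop-out rates, correlations, baseline mean and week-6 means are assumptions, so the percentages show scale and are not a forecast. The change is worth making because it is cheap and rests on a weaker missing-data assumption.

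**What to change.** In Primary analysis: EXP versus TAU, make the primary analysis a linear mixed model for repeated measures of GSI, fitted by likelihood. Include arm, time, arm-by-time and baseline GSI, an unstructured within-patient covariance and a therapist random effect. Include every patient in the analysis set with any available follow-up score, and read the week-12 EXP-TAU contrast from this model.

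Two additions:

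- **Number of sessions.** The article includes it as a covariate in both of its analyses, and the model above does not contain it. Say openly that this changes and give the reason, so that it does not slip in as a side effect.
- **One sensitivity analysis.** Impute drop-outs less favourably by a stated shift (delta) and report whether the conclusion changes.

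The cost is analysis wording only, with no new data or patients. The downside is that the model assumes scores are missing at random and corrects only partly for patients who leave before week 6 (0.243-0.290 instead of 0.300 in the differential scenarios). Patients with no follow-up score at all still add little.

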Taking into account all considerations mentioned before, the research questions for this study are:

1) to examine whether applying immediate feedback at each treatment session in a psychiatric population with severe distress results in better outcomes (10% fewer complaints, enhanced well-being), higher client satisfaction and a more efficient treatment (shorter treatment duration) compared with the no-feedback condition (the same therapists operating in both conditions). Outcome has to be measured with a measure independent from the instrument used in the feedback process.

2) to examine whether applying immediate feedback at each treatment session results in improvements to the alliance; and whether there is a link between any improvement in alliance and improvement in treatment outcome. Alliance to be measured with a measure independent from the instrument to be used for feedback.

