### Randomisation

When entering the treatment facility, patients will be randomly assigned to one of both conditions. Randomisation is performed by a member of the research team before contact with the therapist takes place. There is no assessment for eligibility, all patients referred to the CI&BT team will be included in the study. Though, after the first or second assessment session, a substantial part of the clients is being referred to other services, for instance send to their GP or admitted to a hospital. Only a limited group of clients will be indicated to continue treatment at the CI&BT team. Those who continue treatment after two assessment sessions form the group that is subject to this study. At first contact it is not clear whether a client will be referred to other services or taken into treatment at the CI&BT team, while treatment has already started the moment this becomes clear. As a consequence, only after two sessions it is evident which patients will participate in the definite research condition.

So, a substantial group of randomised patients will be excluded. This post-randomisation exclusion is inevitable, given the nature of the service. Excluding patients from an analysis does not necessarily bias the results, provided that certain requirements are met, for instance that intention-to-treat applies to all randomised patients [49]. Baseline characteristics of all patients, such as gender, ethnicity, education, marital status, diagnosis and level of functioning, shall be analysed to make sure selective exclusion does not bias the results.

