#### Procedures and time points

Initial assessment (the 'baseline measurement') takes place when patients first come into contact with the Crisis Intervention & Brief Therapy Team. The intervention lasts a maximum of six months and stops when treatment ends or after six months.

The PCOMS questionnaires are completed and discussed at every session in the EXP condition. In the TAU condition, every six weeks the ORS form is completed and handed over to a research assistant, without discussing it with the therapist. In both conditions, starting at the time of the baseline measurement, additional questionnaires (BSI, HAQII) are completed by patients in both conditions after 6 weeks, 12 weeks, 18 weeks and 24 weeks of treatment. The therapist also completes questionnaires at the same point in time (6, 12, 18 and 24 weeks after treatment starts) about the course of treatment (CGI) and the alliance (HAQII). When treatment ends, all questionnaires are being completed once again. The follow-up measurement takes place three months after the end of treatment.

Before the study starts, the therapists are required to complete a one-off questionnaire measuring their attitude to the instrument and their motivation with respect to the use of feedback in general. The same questionnaire will be completed by the therapists after the study period.

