#### SRS

A low score on the SRS form may indicate client doubts about the alliance. This need not be a problem when the ORS form indicates that well-being is improving. Therapists are instructed to detect potential breaches in the alliance. Breaches are defined as a score less than 36 in total or less than 9 on any item of the SRS. It is made clear to the client that the SRS score intends to facilitate a conversation about the alliance between client and therapist and that no one has to be offended by the SRS scores since they offer a way for therapists to improve and tailor services based on client preferences.

When a low ORS score fails to rise after a few sessions, the case should be discussed in intervision/supervision or a colleague should be consulted. If better scores still fail to materialise after about seven sessions, referral to another therapist is the appropriate option.

Although therapists will be strongly encouraged to openly discuss the feedback with clients, the frequency or content of these interactions is not formally monitored.

Adherence to the feedback system will be stimulated by regular supervision sessions.

### Outcome questionnaire 45

The Outcome Questionnaire 45 (OQ-45) is a self-report questionnaire developed by Lambert [55] with the aim of mapping out the course of client symptoms during and after the end of the treatment by means of the structural completion of the questionnaire. The list consists of 45 statements leading to three subscales that are aimed at assessing different domains of client functioning: Symptom Distress, Interpersonal Relations and Social Role. Scores are generated for each subscale and the total score is obtained by summing up the three subscores. The internal consistency for the Total score of the Dutch OQ-45 ranges between 0.92 and 0.96 in university, community, patients and community and patients combined samples. For the subscales the consistency is 0.90- 0.95 for the Symptom Distress scale, 0.74-0.84 for the Interpersonal Relations subscale and 0.53-0.72 for the Social Role subscale [56].

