### Naturalistic setting

The fact that this study takes place in a naturalistic setting means that the data collected will be very heterogeneous in several respects. The CI&BT team does not have any threshold and clients are referred through several channels. This means that the population and the diagnostic groups are heterogeneous. The method used for Treatment As Usual is not protocolized because the problems presenting render this impossible: the nature of the problems varies widely, from psychosocial difficulties to personality disorders and psychosis. Psychiatric treatment is required – and this may require compulsory admissions or medical treatment – as well as talking therapy or social support, with contact being either individual or with the system. This means that the treatment method, duration and intensity vary considerably (in both conditions).

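### Both primary models adjust the arm comparison for number of sessions, a post-randomisation variable, so the estimate departs from the intention-to-treat effect if feedback changes that number and sessions track change in GSI

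*Protocol article*

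**What the plan says.** Under Primary analysis: EXP versus TAU, "outcomes of the two treatment conditions will be compared using repeated measures analysis (GLM), with the number of sessions as a covariate". Each follow-up is compared separately with baseline. A multilevel analysis that allows for therapists follows, and there too "The number of sessions will be included as a covariate". No primary model without this covariate is described.

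Four other places bear on the point:
- **Randomisation:** "Randomisation is performed by a member of the research team before contact with the therapist takes place". Every session therefore comes after allocation.
- **Research question 1, at the end of the Background:** feedback is expected to give "a more efficient treatment (shorter treatment duration) compared with the no-feedback condition".
- **Procedures and time points:** "The intervention lasts a maximum of six months and stops when treatment ends or after six months". The number of sessions is thus not fixed by design.
- **Sample size calculation:** power rests on plain GSI means of 1.0 and 1.3 at 12 weeks, and "Analysis will be performed according to the intention to treat principle".

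**The concern.** Randomisation protects the comparison of arms as allocated. It does not protect a comparison of patients who happened to have the same number of sessions, because that number may itself be a result of allocation.

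Adjusting for it can do two things. It can remove any part of the feedback effect that runs through the amount of treatment. It can also bring in an association through unmeasured prognosis, if the way a patient is improving affects how many sessions are given. In either case the arm coefficient no longer answers whether offering feedback gives better outcomes than not offering it, which is research question 1.

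The protocol gives reasons to think that feedback could alter the course of treatment. It hopes for shorter treatment. In the SRS section, feedback scores can also lead to a change in who treats the patient: "If better scores still fail to materialise after about seven sessions, referral to another therapist is the appropriate option". At stake is the headline estimate, which could hide a real effect or suggest one that is absent.

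**Working it through.** **1. The plan's own power figure.** Inputs from Sample size calculation: 90 per arm, one-sided alpha 0.05, difference 0.30 GSI points, SD 0.80.
- Standardised effect: 0.30/0.80 = 0.375.
- Standard error in SD units: √(2/90) = 0.149.
- Power: Φ(0.375/0.149 − 1.645) = 0.81.

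The stated 80% is reproduced. It refers to the plain difference, with no adjustment for sessions.

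**2. The planned model.** I read the comparison of one follow-up with baseline as an analysis of change in GSI. With the covariate, change is regressed on arm and number of sessions. Baseline is therefore already in the model, and the slope that matters is that of *change* on sessions.

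**3. Formula.** Adjusted effect = total effect − (EXP minus TAU difference in sessions) × (within-arm slope of change on sessions). If either factor in the product is zero, there is no bias.

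**4. Assumptions, not in the documents.** Sessions are 0.3 SD lower in EXP. The baseline to week-12 correlation is 0.5, so the SD of change is 0.80 × √(2 × (1 − 0.5)) = 0.80. The within-arm correlation of sessions with change is +0.4 or −0.4.

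**5. Correlation +0.4, true effect −0.375 SD.**
- Adjusted effect: −0.375 − (−0.3)(0.4) = −0.255 SD. The shift of 0.12 SD is 0.096 GSI points, 32% of the planned effect.
- Standard error: 0.149 × √(1 − 0.16) × √(1 + 0.3²/4) = 0.138.
- Power: Φ(0.255/0.138 − 1.645) ≈ 0.58. Simulation gives 0.57, against 0.81 without the covariate.

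**6. Correlation −0.4, no true effect.**
- Adjusted effect: 0 − (−0.3)(−0.4) = −0.12 SD.
- One-sided type I error: Φ(0.12/0.138 − 1.645) ≈ 0.22, and simulation agrees.

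**7. Sessions track only stable severity.** Suppose sessions correlate 0.4 with week-12 GSI, but only through a patient level that is the same at both times. That level cancels in the change score, so the slope is zero. The adjusted effect stays at −0.375 SD. Power is Φ(0.375/(0.149 × 1.011) − 1.645) ≈ 0.80, essentially unchanged.

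**8. Range.** With the SD of change at 0.80, take a session difference of 0.2 to 0.6 SD in either primary scenario and a correlation with change from −0.3 to +0.3. The adjusted effect runs from −0.30 − 0.6 × 0.3 × 0.80 = −0.44 to −0.30 + 0.6 × 0.3 × 0.80 = −0.16 GSI points, against a true −0.30. With no session difference it is −0.30 throughout. The shift in step 5 also depends on the baseline correlation: at 0.3 it is 0.3 × 0.4 × 0.80 × √1.4 = 0.11 GSI points, and at 0.7 it is 0.3 × 0.4 × 0.80 × √0.6 = 0.07.

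**The case against.** The strongest reply has four parts.

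**Duration is not number of sessions.** This stands. The article treats number of sessions and elapsed time as separate factors in its Conclusion, and it separates duration from intensity under Naturalistic setting. A shorter treatment may contain as many sessions. A reader might infer that one variable serves as both outcome and covariate, or that the protocol predicts fewer sessions. The text supports neither. It supports only that feedback may change the number of sessions.

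**Baseline is already in the comparison.** This also stands. A reader might reason from a regression of week-12 GSI on arm and sessions alone, where stable severity would bias the result. That is not the planned model, and step 7 shows that this mechanism does no material harm in it. Bias requires sessions to track change itself. That is plausible where treatment ends according to how the patient is doing, but the documents do not establish it.

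**The authors have a reason to look at sessions.** The Conclusion says that it is hard to separate the effect of sessions from that of feedback, in a setting where treatment varies widely. The interest is legitimate. Adjusting for something that allocation may have changed does not achieve the separation, and no direct-effect aim is stated for the primary comparison.

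**An analysis without sessions exists.** Model 2, under Feedback and client and therapist variation, names pretreatment functioning and no sessions covariate. It is a secondary analysis for a separate paper, so it does not repair the primary one.

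**Conclusion.** The point holds in conditional form. The primary estimate conditions on a variable that arises after randomisation and that feedback may alter. It equals the intention-to-treat effect only if feedback does not change the number of sessions, or if sessions are unrelated to change in GSI within arms. The plan should not depend on either.

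The direction cannot be known in advance. Under the stated assumptions, a true effect of 0.375 SD is estimated as about 0.25 SD with power 0.57, or type I error rises to about 0.22. These figures illustrate possible size. They do not forecast this trial, because the session difference, the correlation with change and the baseline correlation are all assumed.

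A reader might conclude that the main estimate *is* biased. The documents do not support that, since they give no session difference between arms, and with none this bias is absent.

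**What to change.** Remove number of sessions from both the repeated-measures GLM and the multilevel model, and keep the comparison with baseline GSI as planned. Compare number of sessions and treatment duration between arms as outcomes in their own right, which also serves the efficiency part of research question 1. If a sessions-adjusted model is still wanted, label it exploratory and state that it does not estimate the randomised effect.

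The cost is a change of wording in the analysis section. It needs no new data and no extra patients, and the sample size calculation stands because it already refers to the unadjusted difference.

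### The sample size rests on one test (GSI at week 12), but the primary analysis names no outcome, time point or deciding model and contrasts every follow-up with baseline

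*Protocol article*

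**What the plan says.** Three sections of the protocol article bear on this.

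- **Sample size calculation.** The trial is powered for "an effect size of about 0.3 on the Global Severity Index at 12 weeks", with "mean EXP group = 1.0; mean TAU = 1.3; standard deviation at week 12 is 0.80", 90 patients per arm, one-sided alpha 0.05 and 80% power.
- **Primary analysis: EXP versus TAU.** Unspecified outcomes are compared in a repeated-measures GLM. Of that model the text says "In this analysis, each follow-up measurement will be compared separately to the baseline measurement". Because patients are nested within therapists, "these nested data will also be examined in a multilevel analysis, controlling for therapist variation". Neither GSI nor week 12 is mentioned, and the two models are not ranked.
- **Procedures and time points.** The BSI is scheduled at baseline and at weeks 6, 12, 18 and 24. After that, "When treatment ends, all questionnaires are being completed once again", and a follow-up measurement comes three months after treatment ends. That makes up to six post-baseline occasions.

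The first research question, at the end of the Background, lists complaints, well-being, satisfaction and treatment duration. None of them is marked as primary.

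**The concern.** The only scale and time point singled out anywhere are those in the sample size calculation, and the primary analysis does not carry them over. A reader who follows the primary analysis as written obtains a set of contrasts at up to six occasions, on an outcome left open, plus a second model. Nothing states which result decides the trial. A 5% error rate and 80% power describe one test and cannot describe that set.

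The type of contrast also differs. The power calculation compares two week-12 means. The primary analysis contrasts follow-up with baseline, which in a two-arm comparison amounts to comparing changes. The variance is different, so the power is different, and the baseline score is used less efficiently than it could be.

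**Working it through.** **Inputs from the documents.** n = 90 per arm; one-sided alpha 0.05; week-12 means 1.0 and 1.3; SD 0.80; four scheduled on-treatment follow-ups, or up to six with end of treatment and three-month follow-up.

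**Inputs assumed, because the documents give none.** Correlation between test statistics at different occasions, 0.5 to 0.9; correlation ρ between baseline and week-12 GSI, 0.3 to 0.7; baseline SD equal to the week-12 SD.

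**1. The plan's own figure.** The standard error of the mean difference is 0.80 × √(2/90) = 0.119. The ratio 0.30/0.119 is 2.516. Normal power is Φ(2.516 − 1.645) = 80.8%, and the noncentral t gives 80.5%. The stated 80% is reproduced for one test of GSI at week 12.

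**2. Error rate if any follow-up may be claimed.** This is the chance that the largest of k equally correlated normal statistics exceeds 1.645 under no effect (simulation, 1,000,000 draws), for one outcome and one model:

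| Correlation between tests | k = 4 | k = 6 |
|---|---|---|
| 0.5 | 14.4% | 18.7% |
| 0.7 | 12.1% | 14.8% |
| 0.9 | 8.8% | 10.0% |

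The contrasts share one baseline. If all occasions are equally correlated at ρ, two changes from baseline have covariance σ²(1 − ρ) and variance 2σ²(1 − ρ), hence correlation 0.5. That is the first row.

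**3. Contribution of the second model.** With two models tested at one time point and their statistics correlated 0.80 to 0.99 (assumed), the rate rises from 5% to between 7.5% and 5.6%. This is small beside the effect of several occasions.

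**4. Power of the contrast with baseline.** With equal SDs, the variance relative to the week-12 mean comparison is 2(1 − ρ) for the change and 1 − ρ² with baseline as covariate. Noncentral t power at a difference of 0.30 and 90 per arm:

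| ρ | Change: SD used | Power | Covariate: SD used | Power |
|---|---|---|---|---|
| 0.3 | 0.947 | 68% | 0.763 | 84% |
| 0.5 | 0.800 | 81% | 0.693 | 89% |
| 0.7 | 0.620 | 94% | 0.571 | 97% |

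The difference between the two variance factors is 2(1 − ρ) − (1 − ρ²) = (1 − ρ)². It is positive for every ρ below 1 and vanishes as ρ approaches 1.

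**5. Cost of keeping all occasions co-primary.** With Bonferroni, power per occasion for the week-12-type mean comparison is 60.8% at alpha 0.05/4 and 54.8% at 0.05/6. Restoring 80% would take 136 or 149 patients per arm.

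**The case against.** The strongest reply is that the protocol does single out a scale and a time point, in the sample size section, and that the primary analysis merely fails to repeat them. On that view 5% and 80% are sound, the multilevel model is a check for nesting on the same question, and any multiplicity rule may sit in an analysis plan that is not shown. Much of this stands. The figures are right for the test they name. The separate comparisons are stated for the GLM only. No rule that any positive occasion counts as success is written anywhere. The absence of a multiplicity procedure from an article is not held against it here. What remains is that the article does state a primary analysis, and that analysis is not the one powered.

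Four stronger readings are tempting but not supported:

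- *The 5% and 80% figures are invalid.* They hold for GSI at week 12.
- *The error rate is 26%.* That needs six independent tests. The contrasts share a baseline and the same patients. Six is also an upper bound, since the end-of-treatment measurement may coincide with a scheduled visit.
- *The contrast with baseline loses power against the plan.* It does so only below ρ = 0.5. Above that it exceeds the stated 80%, while still trailing covariate adjustment.
- *Complete-case deletion removes about half the patients.* A single repeated-measures GLM over all occasions would drop anyone with a missing visit. But separate comparison can equally mean baseline and one follow-up at a time, which needs only two measurements. The documents give no missingness rate, so the size of the loss cannot be derived.

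**Conclusion.** The point holds as a mismatch between two stated sections: the trial is powered for "on the Global Severity Index at 12 weeks", while its primary analysis fixes no outcome, occasion or deciding model. Read literally, with any follow-up eligible to be the result, the chance of a false positive on one outcome is about 10% to 19% with six occasions and 9% to 14% with four. Leaving the outcome open adds to this by an amount not calculated here. The error-rate range rests on the assumed correlations of 0.9 to 0.5. The power comparison rests on equal SDs and on assumed baseline correlations of 0.3 to 0.7. It shows an avoidable loss of precision at every correlation below 1, and a shortfall against the stated power only at the low end. The second model is a minor source of inflation; what matters there is that the two models are not ranked.

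**What to change.** State one primary test: the arm difference in GSI at week 12, from a single mixed model on all available data, with baseline GSI as covariate and arm, time and arm-by-time terms. Label the repeated-measures GLM, every other occasion and every other scale as secondary.

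Therapist variation needs care. The treatment-as-usual section describes care by the same two therapists where possible, and the Discussion mentions co-therapy pairs and staffing changes. A random term for a single therapist per patient does not fit that structure. Either use a term that allows more than one therapist per patient, or handle therapist in a sensitivity analysis. Whether the number of sessions belongs in the model is a separate question, not settled here.

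The change uses data already scheduled and leaves the planned 90 per arm in place. Apart from working out the therapist term, it is a matter of wording. The downside is that fewer results can be called primary.
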